**Trial Overview**

| Title | Desvenlafaxine for the treatment of hot flashes in women with breast cancer taking Tamoxifen: a randomized, double-blind, placebo-controlled study |
| --- | --- |
| Principal Investigator | [name], PhD  Department of Psychiatry, Seoul National University Hospital |
| Funding agency | Pfizer Ltd. (Investigator-initiated trial) |

| Research Aim | To determine whether desvenlafaxine is effective and safe in treating hot flashes in patients with breast cancer taking Tamoxifen compared to placebo. |
| --- | --- |
| Study design | 4-week dosing, multicenter, randomized, double-blind, placebo-controlled trial |
| Study Period | From IRB Approval Date through December 31st, 2022 |
| Study Participants | Patients with breast cancer taking Tamoxifen and have been experiencing moderate or severe hot flashes at least 14 times per week (an average of 2 or more times per day) for a duration of 1 month or longer. |
| Investigational Drugs | Desvenlafaxine (oral administration, once daily, in two doses: 50mg and 100mg) |
| Sample Size | 339 patients with breast cancer (244 from the primary hospital) |
| Vulnerable research participants | Not applicable |
| Trial Design | # 4-week dosing, multicenter, randomized, double-blind, placebo-controlled study  # Arm 1: Desvenlafaxine 100mg group  First week: one tablet of desvenlafaxine 50mg every morning.  Next three weeks: Two tablets of desvenlafaxine 50mg every morning.  Subsequent three days: One tablet of desvenlafaxine 50mg every morning for gradual tapering  # Arm 2: Desvenlafaxine 50mg group  First week: one tablet of desvenlafaxine 50mg every morning.  Next three weeks: One tablet of desvenlafaxine 50mg plus one placebo tablet every morning.  Subsequent three days: One placebo tablet every morning for gradual tapering.  # Arm 3: Placebo group  First week: one placebo tablet every morning.  Next three weeks: Two placebo tablets every morning.  Subsequent three days: One placebo tablet every morning  # During the study period, participants are required to maintain a daily diary recording their hot flashes symptoms. They will also visit the hospital a total of four times, undergoing four questionnaire assessments and two sets of blood and urine tests.  # Survey Questionnaires  - CGI (Clinical Global Impression), adverse event assessment.  - Hot flashes diary (completed daily)  - EORTC-QLQ-CIPN-20 (peripheral neuropathy).  - MINI (screening for psychiatric disorders)  - PHQ-9 (depression), GAD-7 (anxiety), MDQ (mania)  - PSQI (sleep quality)  - MEQ (morningness-eveningness preference)  - MCTQ (circadian rhythm misalignment)  - FACIT-Fatigue (fatigue)  - FACT-B (quality of life)  - BMQ (Medication Belief Scale), BIPQ (Illness Perception Questionnaire).  - MSPSS (Multidimensional Scale of Perceived Social Support)  - BIS (Body Image Scale)  - CDRS (Connor-Davidson Resilience Scale)  # Blood and urine tests  a) Female sex hormones  - Estrogen, estradiol, progestron, lutenizing hormone (LH), follicle-stimulating hormone (FSH), AMH (Anti-Müllerian hormone)  b) Monoamine metabolites & serotonin receptor  - 5-hydroxyindole acetic acid (5-HIAA), 3-methoxy-4-hydroxyphenylglycol (MHPG)  - Platelet 5HT2A receptor  c) Pro & anti-inflammatory cytokines  - Interleukin-1β (IL-1β), IL-6, IL-12, and IL-18, tumor necrosis factor alpha (TNF-α),  - interferon gamma (IFNγ), granulocyte-macrophage colony stimulating factor (GM-CSF)  - IL-4, IL-10, IL-11, IL-13  d) KNDy peptides  - Kisspeptin, neurokinin B, dynorphin  e) Calcitonin gene‐related peptide (CGRP)  f) Serum lipid profile, Urinalysis  g) genetic polymorphism in estrogen receptors (ESR1 PvuII; rs#2234693 and XbaI; rs#9340799 and ESR2-02; rs#4986938) and serotonin transporter gene (SLC6A4; rs#11080121)  h) Urinalysis |
| Efficacy evaluation | # A self-reported hot flush diary completed daily  - The daily occurrence of hot flashes and their severity, rated on a scale from 1 (mild) to 4 (very severe), are recorded together.  - The daily hot flush score is derived by multiplying the frequency of symptoms by their severity. The average score over a week is then computed, and after 4 weeks of treatment, the efficacy of desvenlafaxine in reducing hot flash symptoms is evaluated in terms of both presence and degree of reduction. |
| Safety evaluation | Adverse events, lipid tests, and urine tests |
| Expected impacts and anticipated results | While hot flashes in the general population can often be treated with hormonal therapy, this approach is not viable for breast cancer patients specifically, as the use of hormonal therapy can increase the risk of further cancer progression.  Desvenlafaxine does not affect cancer progression and shows no drug interactions with Tamoxifen, making it safe for use. Consequently, it holds promise as an effective treatment for hot flashes in breast cancer patients on Tamoxifen.  This study is a randomized, double-blind, placebo-controlled trial designed to evaluate the efficacy of Desvenlafaxine as an alternative to hormonal therapy in these patients.  Additionally, through blood tests for estradiol, FSH, and AMH, as well as association analyses with the estrogen receptor gene and serotonin transporter gene, we aim to establish a biological foundation for predicting risk factors and treatment responses to hot flashes in breast cancer patients on Tamoxifen. |

**1) Background**

Tamoxifen is commonly used as adjuvant treatment after surgery and chemotherapy for early and advanced estrogen receptor positive (ER-positive) breast cancers. Tamoxifen blocks the role of estrogen in the body, a common side effect is hot flashes, a symptom of menopause in premenopausal women, and worsening of hot flashes in postmenopausal women. Hot flashes reduce the quality of sleep in patients with breast cancer and make them more tired, thereby reducing their overall quality of life [1].

Hormone therapy using estrogen and progesterone is the most effective treatment for hot flashes. However, in women with breast cancer, these hormonal treatments can be potential risk factors for breast cancer progression and are not commonly used. Therefore, there is a need for alternative hormone therapies to control hot flashes in women with breast cancer taking tamoxifen.

Antidepressants (Selective Serotonin Reuptake Inhibitors, SSRIs; Serotonin and norepinephrine reuptake inhibitors, SNRIs), Gabapentin, and Clonidine have been studied as non-hormonal treatments for hot flashes in women with breast cancer. Among these, venlafaxine (SNRI), Paroxetine (SSRI), and Gabapentin have been reported as promising non-hormonal treatments for hot flashes in patients with breast cancer [2]. However, most of these are accompanied by various side effects such as nausea, fatigue, dry mouth, constipation, drowsiness, and insomnia. Furthermore, paroxetine reduces the anticancer effect of Tamoxifen on drug interactions by affecting Cytochrome P450 2D6 (CYP2D6) metabolism in the liver. Gabapentin had no additive effect on depressive symptoms accompanied by hot flashes in patients with breast cancer. Therefore, there is an urgent need to develop non-hormonal therapies that are effective, have few side effects, and are safe for cancer treatment to improve hot flashes in these patients.

Desvenlafaxine is an SNRI antidepressant that is considered a non-hormonal treatment.

**2) Objectives Of the study**

Desvenlafaxine is the main active metabolite of Venlafaxine, and has fewer side effects and drug interactions than Venlafaxine. In previous studies, desvenlafaxine 100 mg had no effect on CYP2D6 metabolism and no pharmacokinetic drug interactions with tamoxifen [3].

Desvenlafaxine has been shown to reduce the frequency and severity of hot flashes in several randomized controlled clinical trials in postmenopausal women [4]. In these studies, desvenlafaxine, starting at 50 mg and titrating up to 100 mg, was effective in improving menopausal hot flashes by 55-69%, was safe, and had few side effects. Therefore, desvenlafaxine can be considered an effective and safe treatment for hot flashes in patients with breast cancer taking tamoxifen. Presently, no clinical trials have been conducted as in this study in desvenlafaxine.

This was a 4-week, multi-centre, randomized, double-blind, placebo-controlled study of desvenlafaxine 50 mg and 100 mg to determine whether it is effective in reducing the number and severity of hot flashes in breast cancer patients taking tamoxifen.

1. **Investigational drugs**

**1) Product name**

- *Pristiq* (Active ingredient: Desvenlafaxine 50 mg per tablet; Pale pink, square, one side pyramid-shaped, with sustained-release film coating.)

**2) Placebo**

- Starchy tablet, identical in appearance to *Pristiq*

1. **Inclusion criteria, exclusion criteria, number of study participants targeted and rationale for calculation**
2. **Inclusion criteria**

- Women, age 19 years or older
- Diagnosed with atypical ductal hyperplasia, ductal carcinoma in situ, lobular carcinoma in situ, or invasive breast adenocarcinoma stages I through IV.
- Taking tamoxifen regularly (6+ times/week) following the termination of surgery, chemotherapy, and/or radiation therapy due to breast cancer
- Moderate to severe hot flashes occurring 14+ times/week (on average, 2+ times/day) lasting for more than a month.

1. **Exclusion Criteria**

- Pregnant or breastfeeding
- History of seizure or hepatic/renal dysfunction
- Receiving any hormone therapy (including estrogen-/progesterone-/androgens-containing agents) or taking corticosteroids
- Use of antidepressants such as gabapentin, pregabalin, or clonidine to address depression and/or hot flash symptoms.
- Currently suffering from or having a history of severe psychiatric symptoms, such as hallucinations and delusions, mania, and high suicide risk

1. **Number of participants targeted and rationale for calculation**

This study aimed to determine whether the use of desvenlafaxine in patients suffering from hot flashes reduces its symptoms.

The primary endpoint was defined as the percentage reduction in hot flush symptoms = (symptom score at week 4–symptom score at a week before treatment) / symptom score at a week before treatment), and the following assumptions were made to calculate the number of participants to fulfil the primary outcome of the study.

① Level of significance, α = 0.025

The study was divided into three groups (50 mg, 100 mg, placebo), and a type 1 error was defined as 0.025 to determine whether there was a significant difference between the Desvena 50 mg treatment group vs. the placebo group and the 100 mg treatment group vs. placebo group.

② Type II error (β) is set to 0.20, and the power of the test is maintained at 80%.

③ The hypotheses in this study are as follows (two-tailed test):

- Null hypothesis: There is no difference in the rate of reduction of hot flashes between the 50 mg vs. placebo groups or between the 100 mg vs. placebo groups.
- Alternative hypothesis: There is a difference in the rate of reduction of hot flashes between the 50 mg versus placebo or 100 mg versus placebo groups.

The number of participants was calculated based on a comparison of the desvenlafaxine 100 mg group with the placebo group. In a similar study conducted previously on menopausal women complaining of hot flashes, the mean reduction rate was 0.8 and standard deviation (SD) 0.72 when desvenlafaxine 100 mg was administered, and in the case of the placebo group, the average reduction rate was 0.47 and standard deviation 0.79 [5]. The number of participants in the study that achieved 80% power at a 2.5% significance level was 101 in each arm, for a total of 303. The number of participants was planned to be 339 to account for a dropout rate of 10 %.

1. **Study participant recruitment plan**

Participants will be recruited by posting the [Notice of Recruitment of Research Subjects] in the outpatient departments of the haematology oncology and integrated care center, surgery, obstetrics/gynecology, and mental health clinic. In addition, participants will be recruited by posting a recruitment announcement on “https://cafe.naver.com/uvacenter/158559", the representative internet community of the Breast Cancer Patients' Association.

The principal investigator and funding agency will not exclude patients from participation in this study based on race or socioeconomic status. If the selection criteria for this study were met, every effort will be made to allow as many patients as possible to participate in this study.

1. **Study methods**
2. **Specific research methods**

|  | Baseline | Medication Period | | End of Medication | Tapering period |
| --- | --- | --- | --- | --- | --- |
| Period | T0 | T1 | T2 | T3 | 3days |
| Week | -1w | 0w | 1w | 4w | 4w + 3days |
| Day |  | 1 | 8 | 29 | 29–31 |
| Permissible range of visits |  | ±3 days | ±3 days | ±3 days |  |
| Informed consent | O |  |  |  |  |
| Randomization |  | O |  |  |  |
| Study Drug Administration |  | O | O |  |  |
| Medical record check | O |  |  |  |  |
| Physical Examination |  | O | O | O |  |
| Hot flashes diary | O | O | O | X |  |
| Self-reported questionnaires | O | O | O | O |  |
| Blood/urine tests |  | O |  | O |  |
| Assessment of adverse events |  | O | O | O |  |
| Medication adherence evaluation |  |  | O | O |  |
| Concomitant medication check | O | O | O | O |  |

This was a 4-week dosing, multicenter, randomized, double-blind, placebo-controlled trial.

Participants will be randomized to receive desvenlafaxine or placebo for a total of 4 weeks + 3 days, maintain a daily hot flashes diary, and have a total of 4 clinic visits for four questionnaire assessments and two blood and urine tests. Height, weight, BMI, and blood and urine tests will be performed at T1 and T3.

The participants will complete an informed consent form at the initial visit, and an initial questionnaire assessment will be administered. If participants did not know the exact date of menstruation in the menstrual history assessment section and the date of breast cancer diagnosis in the cancer-related information section, the following are written: if participants remember only the month, write 15 days (e.g., October ?day 2017 -> October 15, 2017), and if participants remember the beginning, middle, and end of the month instead of the exact date, write 5, 15, and 25 days, respectively (e.g., early October 2017 -> October 05, 2017).

Afterwards, the participants are advised to maintain a hot flashes diary without medication for one week to assess the baseline status before medication. During the same period, patients will be randomized into the desvenlafaxine 100 mg, 50 mg, or placebo group by a third-party institution unrelated to the study (Medical Research Collaborating Center).

From one week after study registration, each of the three groups will be administered a dose of desvenlafaxine or placebo for four weeks. To reduce the adverse effects of abrupt discontinuation in the desvenlafaxine 100 mg group, there will be a 3-day tapering period with one tablet of desvenlafaxine 50 mg or one tablet of placebo.

During the administration period, the patients will complete a hot flashes diary and medication compliance assessments. After participating in the study, patients will receive a hot flashes diary form to record for 1 week, 1 week, and 3 weeks, at visits of -1, 0, and 1 week, and the data written by the patient during that period will be included in the case report form of the previous periods. During the above visits, a physical examination and assessment for adverse events and medication adherence will be performed.

Self-reported questionnaire assessments will be administered at visits 1 week prior to study enrollment and 0, 1, and 4 weeks after study enrolment. Moreover, blood and urine tests will be performed at 0 and 4 weeks after study enrollment.

1. **Control group setting and randomization method**

Participants who provided written informed consent and fulfilled all inclusion and exclusion criteria for enrollment will be randomized in a 1:1:1 ratio to the desvenlafaxine 100 mg arm, desvenlafaxine 50 mg arm, and placebo arm.

A randomization table will be created to assign the participants to one of the three arms using a stratified block randomization method, and web-based allocation will be made according to the randomization table. The stratification factors are age (< 50 and >50 years), presence of depression (defined as a PHQ-9 score of 9 or more), and institution (Seoul National University, Seoul National University Bundang Hospital, National Cancer Center). The randomization table and web-based randomization will be managed and operated by the Medical Research Collaborating Center (MRCC) of Seoul National University/Seoul National University Hospital, which is independent of the study.

If a serious adverse reaction occurs in a participant after participating in the study, they will be withdrawn from the study and unblinded; in this case, the investigator will unblind the participant through a third-party institution (Medical Research Collaborating Center) that manages and operates the randomization.

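### The antidepressant exclusion misclassifies its example drugs and is limited by indication, so women taking hot-flash treatments named in the protocol for another reason remain eligible

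*Protocol*

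**What the plan says.** The drug exclusion in the Exclusion Criteria reads "Use of antidepressants such as gabapentin, pregabalin, or clonidine to address depression and/or hot flash symptoms". The criterion just before it, on hormones and steroids, carries no limit by indication: "Receiving any hormone therapy (including estrogen-/progesterone-/androgens-containing agents) or taking corticosteroids".

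The Background groups the drugs differently: "Antidepressants (Selective Serotonin Reuptake Inhibitors, SSRIs; Serotonin and norepinephrine reuptake inhibitors, SNRIs), Gabapentin, and Clonidine have been studied as non-hormonal treatments for hot flashes". It then says that "venlafaxine (SNRI), Paroxetine (SSRI), and Gabapentin have been reported as promising non-hormonal treatments for hot flashes in patients with breast cancer", and of gabapentin and mood that "Gabapentin had no additive effect on depressive symptoms accompanied by hot flashes in patients with breast cancer".

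The Objectives section describes desvenlafaxine as the main active metabolite of venlafaxine.

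The visit schedule under Specific research methods has a row "Concomitant medication check", marked at T0, T1, T2 and T3, and a medical record check at T0. Neither is tied to a list of prohibited drugs.

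**The concern.** There are two defects in one sentence.

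- **Class label.** Three drugs are offered as examples of antidepressants, and no SSRI or SNRI is named. Site staff cannot tell from the examples what the class is meant to cover.
- **Purpose clause.** Use counts only if it is for depression or hot flashes. The same drug taken for pain, neuropathy, anxiety or blood pressure does not exclude.

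The trial is likely to meet such women. Entry follows surgery, chemotherapy or radiotherapy. Neuropathy is among the measured outcomes ("EORTC-QLQ-CIPN-20 (peripheral neuropathy)"), as is anxiety (GAD-7), and the recruitment plan includes the mental health clinic.

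At stake is how clean the placebo comparison is. If some women in every arm already take a drug that works on hot flashes, the contrast may shrink and vary more. Placebo participants on venlafaxine would not be unexposed controls. Three sites reading an unclear criterion may also admit different women.

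**Working it through.** **Step 1. Does the label conflict with the rest of the protocol?** In the Background, antidepressants are spelled out as SSRIs and SNRIs, and gabapentin and clonidine follow as separate items. Gabapentin is also said to add nothing for depressive symptoms. The Exclusion Criteria make gabapentin and clonidine examples of antidepressants. The two sections conflict. Pregabalin appears only in the exclusion.

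**Step 2. Who remains eligible under the literal wording?**

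| Drug and reason | What the protocol says of the drug | Excluded as written? |
|---|---|---|
| Venlafaxine for depression | Promising for hot flashes; parent of the study drug | Yes |
| Venlafaxine for anxiety | Same | No |
| Paroxetine for anxiety | Promising for hot flashes | No |
| Gabapentin for hot flashes | Promising for hot flashes | Yes |
| Gabapentin for neuropathy | Same | No |
| Clonidine for blood pressure | Studied for hot flashes | No |

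**Step 3. Does anything else close the gap?** No. The other exclusions do not mention these drugs. The medication check records use but states no consequence. Under Specific research methods, the instruction to keep the diary for a week without medication describes the baseline week before study drug; it is not an eligibility rule or a stated washout. Reading the criterion as a garbled list (antidepressants, gabapentin, pregabalin or clonidine) mends the label but leaves the purpose clause in force.

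**Step 4. How large could dilution be?** First, the plan's own sample size.

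- Inputs from the sample-size section: mean reduction 0.80 (SD 0.72) on 100 mg, 0.47 (SD 0.79) on placebo; two-sided α = 0.025; power 80%.
- Difference = 0.80 − 0.47 = 0.33.
- SD = √[(0.72² + 0.79²)/2] = 0.756, so the standardised difference is 0.33/0.756 = 0.437.
- The two-sample t-test needs 100.99, that is 101 per arm, as stated. Then 101/0.90 = 112.2, rounded up to 113, and 3 × 113 = 339, as stated. Power at 101 per arm is 80.0%, so there is no margin.

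Now let a proportion *w* of women take such a drug and let the treatment difference in them be reduced by a fraction *a*. The average difference is 0.33 × (1 − *w* × *a*). With 101 per arm, SD held at 0.756 and the noncentral t distribution:

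| *w* | *a* | Difference | Power |
|---|---|---|---|
| any | 0 | 0.330 | 80.0% |
| 2% | 25% | 0.328 | 79.6% |
| 5% | 25% | 0.326 | 78.9% |
| 5% | 50% | 0.322 | 77.8% |
| 10% | 50% | 0.314 | 75.4% |
| 20% | 50% | 0.297 | 70.3% |
| 10% | 100% | 0.297 | 70.3% |

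Both *w* and *a* are assumptions; the protocol gives neither.

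**The case against.** **The label is only an editorial slip.** Largely true. The three drugs are named, so they are excluded for the stated purposes whatever they are called, and the intended list is easy to guess. The limit by indication survives that reading.

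**The purpose clause may be deliberate.** The recruitment plan aims to let as many eligible patients as possible take part, and a broader population is a legitimate choice. But the protocol gives no reason for the clause, and its neighbouring exclusion has none.

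**Dilution is assumed, not shown.** This stands. The endpoint is percentage change from each woman's own pre-treatment week, and every entrant must still have at least 14 moderate or severe hot flashes a week. A stable background drug is already reflected in her baseline. If desvenlafaxine's proportional effect is unchanged in her, power is unaffected.

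A reader might also infer more than the documents support:

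- *That background drug changes are confounded with study drug.* Allocation is randomized and double-blind, so such use is balanced between arms on average.
- *That all the listed drugs act on hot flashes.* The Background calls only venlafaxine, paroxetine and gabapentin promising. Clonidine is merely among those studied, and pregabalin is not mentioned there.
- *That the wording creates a hazard from combining serotonergic drugs.* No section discusses this, and the point does not rely on it.

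**Conclusion.** The point holds as a defect in a stated eligibility rule. The criterion contradicts the Background's drug classes, and its purpose clause admits women who take, for another reason, drugs that the protocol itself presents as promising for hot flashes. The clearest case is venlafaxine: by the protocol's own account, a placebo participant taking it for anxiety would carry the study drug's active substance.

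The expected consequences are a weaker contrast, more variability and inconsistent admission across sites; systematic bias between arms is not expected. The size is uncertain. Halving the effect in 5% to 20% of women would cost about 2 to 10 percentage points of power from a design with none to spare, while small or unblunted background use would cost almost nothing. How many such women would enrol cannot be learned from the document.

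**What to change.** Reconcile the Exclusion Criteria with the Background. Name antidepressants (SSRIs and SNRIs), gabapentin, pregabalin and clonidine as separate entries. Remove the dependence on indication at least for the drugs the protocol itself describes as hot-flash treatments, or keep it and state why. Apply the criterion at T0, where the medical record and concomitant medication checks are already scheduled.

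This needs a wording amendment and no new procedure. The downside is a slightly smaller recruitment pool, mainly women treated for neuropathy, anxiety or blood pressure.

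### Testing each dose at a fixed two-sided 0.025 is valid, but Holm's step-down would give more power for a second dose within the same 5% family-wise bound (optional gain, not an error)

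*Protocol*

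**What the plan says.** The Protocol section on the number of participants and its rationale gives "Level of significance, α = 0.025". It explains that, with three groups, "a type 1 error was defined as 0.025 to determine whether there was a significant difference" for 50 mg against placebo and for 100 mg against placebo. The hypotheses are two-tailed and cover both comparisons. The alternative is worded with an *or* between the doses.

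On sizing, the same section states that "The number of participants was calculated based on a comparison of the desvenlafaxine 100 mg group with the placebo group". Its inputs are that "the mean reduction rate was 0.8 and standard deviation (SD) 0.72 when desvenlafaxine 100 mg was administered" and, for placebo, "the average reduction rate was 0.47 and standard deviation 0.79". The result is "80% power at a 2.5% significance level was 101 in each arm, for a total of 303", raised to 339 for 10% dropout. No effect or SD is given for 50 mg. Allocation is 1:1:1.

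The text shown does not name Bonferroni, an overall 5%, or any rule that lets one comparison's level depend on the other's result.

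**The concern.** A fixed 0.025 for each of two comparisons is the Bonferroni split of 0.05. Holm tests the smaller p-value at 0.025 and, only if that is significant, tests the other at 0.05. Its family-wise error is also at most 0.05, and it can only add rejections.

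The objectives name both doses, so a conclusion on the second dose has value. The 50 mg comparison has no stated power. If its effect is smaller than that of 100 mg, it is the one more likely to fall between 0.025 and 0.05 and be lost under the fixed split. What is at stake is some power for that second conclusion. The validity of the trial is not in question.

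**Working it through.** **Inputs from the protocol.** Mean reduction 0.80 (SD 0.72) on 100 mg and 0.47 (SD 0.79) on placebo; 101 evaluable patients per arm; two-sided 0.025 per comparison.

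**Inputs assumed.** The 50 mg SD is set to 0.72, and the 50 mg effect is varied from 0 to 0.33.

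**1. The plan's own figure.** Difference = 0.80 − 0.47 = 0.33. Average variance = (0.72² + 0.79²)/2 = (0.5184 + 0.6241)/2 = 0.57125, so SD = 0.756.

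n per arm = 2 × (z₀.₉₈₇₅ + z₀.₈₀)² × SD²/difference² = 2 × (2.241 + 0.842)² × 0.57125/0.1089 ≈ 99.7, so 100 by the normal formula. The noncentral t calculation gives 101, with power 80.0%. Dropout: 101/0.90 rounds up to 113, and 3 × 113 = 339. The stated figures are reproduced, which confirms two-sided 0.025 as the level used.

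**2. What the level costs.** Standard error at 101 per arm = √(1.1425/101) = 0.1064, so the expected z is 0.33/0.1064 = 3.10. Power at two-sided 0.025 is Φ(3.10 − 2.24) = 80.5%. At two-sided 0.05 it is Φ(3.10 − 1.96) = 87.3%.

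**3. Error bound under Holm.** If both nulls are true, any rejection needs the smaller p-value at or below 0.025, which has probability at most 2 × 0.025 = 0.05. If one null is true, a false rejection needs that p-value at or below 0.05. Either way the bound is 5%.

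**4. Simulation.** Four million trials per row, normal test statistics, shared placebo arm, 100 mg effect 0.33. Each cell shows fixed split → Holm.

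| Assumed 50 mg effect | 50 mg significant | 100 mg significant | Both | At least one |
|---|---|---|---|---|
| 0 (false claim for 50 mg) | 2.5% → 4.2% | 80.6% → 80.7% | 1.6% → 3.4% | 81.5%, same |
| 0.10 | 9.7% → 15.3% | 80.6% → 80.7% | 9.5% → 15.1% | 80.8%, same |
| 0.20 | 35.9% → 45.5% | 80.6% → 81.5% | 34.0% → 44.6% | 82.5%, same |
| 0.25 | 54.4% → 63.1% | 80.5% → 82.6% | 50.0% → 60.8% | 84.9%, same |
| 0.33 | 80.6% → 85.0% | 80.6% → 85.0% | 70.0% → 78.8% | 91.1%, same |

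With neither dose active, the chance of any false claim is 4.6% under both rules.

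**5. Reading the table.** From the unrounded results, the 50 mg gain is 5.6, 9.6, 8.8 and 4.4 points at effects of 0.10, 0.20, 0.25 and 0.33. The 100 mg gain over the same effects runs from 0.1 to 4.4 points. The gain for both doses is 8.8 to 10.8 points at effects of 0.20 to 0.33.

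Every extra Holm rejection occurs in a trial where one dose has p at or below 0.025 and the other lies between 0.025 and 0.05. In those trials the second dose's 97.5% interval includes zero. That is 78.8% − 70.0% = 8.8% of trials at a 50 mg effect of 0.33, and 10.9% at 0.22.

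**The case against.** **The 0.025 is only a sizing assumption, and the testing rule belongs in the SAP.** This stands in part. The level is introduced among the sample-size assumptions, the SAP is not shown, and the lack of a multiplicity section in the protocol is no finding. The sentence does, however, name both comparisons and tie 0.025 to judging whether a significant difference exists, so it also reads as a testing level. An SAP that used Holm would fit the sizing but would differ from that sentence.

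**Nothing is wrong.** This stands. A two-sided 0.025 each is valid, conservative and consistent with 101 per arm. Other valid procedures exist, such as step-down Dunnett or a fixed sequence.

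**The fixed split does buy something.** This stands. A reader might infer that it gains nothing in error control. That is true only of the 5% bound. With 50 mg inactive and 100 mg at 0.33, false claims for 50 mg occur in 2.5% of trials under the fixed split and 4.2% under Holm.

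**There is no gain on the hypothesis as worded.** The alternative joins the doses with *or*, and the chance of showing at least one dose is identical under both rules. The gain is confined to conclusions on a second dose. The objectives name both doses, which is why it still has value.

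**The 50 mg figures rest on inputs the protocol does not give.** This stands, so only a range can be quoted. A single figure, such as the rise from 43% to 53% at an assumed effect of 0.22, lies near the top of that range and should not be read as the expected gain.

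**Conclusion.** The point holds as an optional efficiency gain. At 101 per arm and within the same 5% family-wise bound, Holm adds about 4 to 10 points of power for 50 mg (assumed effects 0.10 to 0.33), 0.1 to 4.4 points for 100 mg, and about 9 to 11 points for both doses together (50 mg effects 0.20 to 0.33).

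These sizes rest on the protocol's means and SDs for 100 mg and placebo, on a 50 mg SD assumed to be 0.72, and on an overall 5% inferred from 0.025 for each of two comparisons. That Holm never rejects less than the fixed split needs none of these assumptions about effects or SDs.

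Two stronger readings are tempting, and the protocol supports neither. One is that the multiplicity handling is an error: the split is valid and the sample size is right for it. The other is that Holm would allow a smaller trial: the 100 mg comparison still needs 80% power at 0.025 if it is to succeed on its own at the first step, so 101 per arm remains.

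**What to change.** If the team wants the gain, replace the per-comparison testing level with wording such as: *The family-wise error is two-sided 0.05, controlled by Holm's procedure: the smaller p-value is tested at 0.025 and, if significant, the other at 0.05.* Keep 0.025 in the sample-size calculation, and use the same wording in the SAP.

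Add that the Holm-adjusted p-value decides significance. If 97.5% intervals are reported, a dose significant only at the second step will have an interval that includes zero (about 9 to 11% of trials at 50 mg effects of 0.22 to 0.33), and the report should explain this.

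The change must be fixed before unblinding, because it makes the rule more permissive. If that is no longer possible, the fixed 0.025 should stay.

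The cost is a sentence or two in the protocol and SAP, with no added patients, visits or data. In return the team accepts a higher risk of a false claim for the second dose when only one dose works (2.5% to about 4.2%, still under 5%) and intervals that do not always match the test.
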